## Abstract

**Background:**

Ruptured aneurysms, the commonest cause of nontraumatic subarachnoid hemorrhage, can be catastrophic; the mortality and morbidity of affected patients being very high. Some risk factors, such as smoking, hypertension and female sex have been identified, whereas others, such as hemodynamics, imaging, and genomics, remain unclear. Currently, no accurate model that includes all factors for predicting such rupture is available. We plan to use data from a large cohort of Chinese individuals to set up a multidimensional model for predicting risk of rupture of unruptured intracranial aneurysms (UIAs).

**Methods:**

The China Intracranial Aneurysm Project-2 (CIAP-2) will comprise screening of a cohort of 500 patients with UIA (From CIAP-1) and focus on hemodynamic factors, high resolution magnetic resonance imaging (HRMRI) findings, genetic factors, and biomarkers. Possible risk factors for rupture of UIA, including genetic factors, biomarkers, HRMRI, and hemodynamic factors, will be analyzed. The first project of the China Intracranial Aneurysm Project (CIAP-1; chaired by the Department of Neurosurgery, Tangdu Hospital, Fourth Military Medical University, Xi’an, Shaanxi, China) will prospectively collect a cohort of 5000 patients with UIA from 20 centers in China, and collect baseline information for each patient. Multidimensional data will be acquired in follow-up assessments. Statistically significant clinical features in the UIA cohort will also be analyzed and integrated into the model for predicting risk of UIA rupture. After the model has been set up, the resultant evidence-based prediction will provide a preliminary theoretical basis for treating aneurysms at high risk of rupture.

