### Data collection and management

The following patient characteristics will be collected and recorded: (1) basic clinical characteristics; (2) relevant data concerning personal and family history; (3) relevant imaging findings; (4) findings of head HRMRI, computational fluid dynamics (CFD) testing, and relevant genetic testing; (5) relevant laboratory findings; and (6) neurological function-related scores on admission or first visit. The following characteristics of aneurysms will be collected and recorded: size, neck size, dome-to-neck ratio, dome-to-artery ratio, shape, location, clinical presentation, and number of aneurysms.

The follow-up data collected will comprise: (1) frequency and number of follow-up assessments; (2) findings on general evaluation; (3) deaths; (4) imaging findings; (5) UIA growth (assessed by repeated imaging to avoid treatment bias); and (6) life-style changes. Throughout, neurobehavioral-related scores will include: (1) Glasgow Coma Scale scores; (2) improved RANKIN scale scores (somatic changes); and (3) Mini-Mental State Examination scores (psychological changes).

The participants will initially be followed up three times: at 90 ± 14 days, 180 ± 30 days, and 365 ± 30 days and at least annually for a minimum of 5 years thereafter. Participation in the study will end if rupture occurs. Patients with SAH will be transferred to the CIAP-5 project (a study of emergency treatment of aneurysmal subarachnoid hemorrhage; CIAP-5, the fifth project of the China Intracranial Aneurysm Project, is managed by Xuanwu Hospital, Capital Medical University, Beijing, China). In addition, patient’s relatives are requested to report sudden deaths to the study group. In such instances, autopsies will immediately be organized in study hospitals and tissue samples of ruptured aneurysms will be supplied to the project for analysis, subject to the informed consent of the participants’ relatives.

Formal training, including investigator training and familiarization with the study protocol, will be initiated. An inspection team of experts drawn from various organizations will follow participants up with the specified regular monitoring until the end of the study period. All data will be collected on paper Case Report Forms (CRF), then input into Electronic Data Capture (EDC) for management, and retained for 5 years after the end of the study. The accuracy and rigorousness of the data will be checked in a timely manner.

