### Model building (first set of UIA queues)

The following possible or established risk factors for UIA will be collected and analyzed: age; sex; blood pressure, smoking, alcohol consumption, hyperlipidemia, diabetes mellitus, and family history of subarachnoid hemorrhage, intracranial aneurysm, and autosomal dominant diseases (polycystic kidney, Marfan syndrome, collagen dysplasia, etc.)The following imaging data will be collected and analyzed: shape, location, size, aspect ratio and odds ratio of aneurysms, morphological factors such as the angle of the aneurysm jet, and known risk factors for rupture.In our experience, follow-up angiography alone does not adequately predict the outcome whereas HRMRI is a more useful means of following these lesions [38]. We have also found and reported that aneurysm wall enhancement on HRMRI predicts instability of an intracranial aneurysm [39]. HRMRI will be performed on patients enrolled in the UIA follow-up cohort at the 20 participating centers and HRMRI-identified aneurysm wall enhancement assessed as a possible predictor of UIA rupture. Two-dimensional short-axis images of the aneurysms generated from the registered pre-and post-contrast T1w-SPACE images will be used to identify wall enhancement [13].To identify risk factors, the nested cohort study will incorporate the following: incidence of aneurysm rupture in the follow-up cohort, the definition of UIA recently rupture before the duration of follow-up was high risk of rupture of UIA, acquisition of imaging data for hemodynamic calculations; according to the aneurysm ratio of 1:2 UIA (rupture vs non-rupture), and analysis of differences in hemodynamic variables, genetic factors, and biomarkers.A.Analysis of hemodynamic variables: A three-dimensional shape will be created and image data from computed tomographic angiography, magnetic resonance angiography, or DSA saved as DICOM files. Once the 3D model has been reconstructed, it will be saved in an STL file format. A rigid wall in the parent vessel and aneurysm will be assumed in the simulation of hemodynamics. We will start by using ANSYS ICEM CFD (Materialise, Leuven, Belgium) to build a finite element model, then perform a simulation on ANSYS CFX software (Materialise), and finally use ANSYS CFX POST postprocessing to calculate Wall Shear Stress (WSS), maximum wall shear stress (WSSmax), low WSS areas, steady state of blood flow, and so on. Our team has already identified that these factors are associated with the stability of aneurysms [40–42].B.Gene and biomarker analysis: Blood samples will be collected from all participants and specimens of the aneurysm wall from patients who undergo craniotomy. Target chromosomes will be tested for blindly. Target genes and biomarkers identified as possibly relevant by the latest international research will be tested. Differences in genes and biomarkers between rupture and non-rupture groups will be compared to identify rupture-related factors.

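### The article gives conflicting times for measuring the time-varying predictors (HRMRI, hemodynamics, morphology, non-genetic biomarkers) and sets no common time for ruptured and non-ruptured aneurysms

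*Protocol article*

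**What the plan says.** Three places bear on timing.

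- **Abstract, Methods.** CIAP-1 is to enrol the cohort "and collect baseline information for each patient". The next sentence reads "Multidimensional data will be acquired in follow-up assessments". Taken together, these put the multidimensional predictors after baseline.
- **Model building.** The nested comparison starts from the ruptures seen in the cohort and continues: "the definition of UIA recently rupture before the duration of follow-up was high risk of rupture of UIA, acquisition of imaging data for hemodynamic calculations". It then compares ruptured with non-ruptured aneurysms at 1:2. No index time is given for the non-ruptured ones. For HRMRI the section says only that "HRMRI will be performed on patients enrolled in the UIA follow-up cohort at the 20 participating centers". Blood is to be taken from all participants, also with no time stated.
- **Data collection and management.** The list of patient characteristics includes "findings of head HRMRI, computational fluid dynamics (CFD) testing, and relevant genetic testing" and laboratory findings. Its last item is "neurological function-related scores on admission or first visit". Follow-up data form a separate list, which names imaging and aneurysm growth but not HRMRI, CFD, genes or biomarkers.

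The inclusion criteria require the aneurysm to be confirmed by CTA, MRA and/or DSA, so every patient has angiography at entry.

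**The concern.** The model is meant to help identify unruptured aneurysms at high risk of rupture. Its user will enter values from the first work-up, so its coefficients and cut-offs should be estimated from values of that kind. If a ruptured aneurysm contributes its last measurement before the event and a non-ruptured one contributes a measurement from any visit, part of the difference between the groups comes from when they were measured.

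The protocol itself expects these quantities to move. Its background says that flow alters the shape of the aneurysm on the way to rupture, and its follow-up tracks growth by repeated imaging.

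The validation group would not expose the problem. It is one third of the same cohort and would be measured under the same rule.

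**Working it through.** **1. The texts side by side**

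| Section | Time for HRMRI, CFD and biomarkers | Time for comparators |
|---|---|---|
| Abstract, Methods | Follow-up assessments | Not separated |
| Model building | Hemodynamic imaging: apparently shortly before rupture. HRMRI and blood: none stated | None stated |
| Data collection and management | Readable as admission or first visit | Same list |

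These cannot all hold, and no section states one time for both groups.

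**2. Is rupture status known when the nested set is chosen?**

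Inputs: 1% annual rupture rate, 4 years, 5000 patients, 2:1 split, at least 130 ruptures in the modeling group, 20% loss, 500 to enrol, 1:2 ratio.

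- Ruptures in the modeling group: 5000 × 0.01 × 4 × 2/3 = 133.3. This matches the stated 130 if no loss is taken off.
- A 1:2 nested sample: 130 × 3 = 390, and 390 / 0.80 = 487.5, so 488. This is within 3% of the stated 500.
- If the 500 were instead chosen at entry: 500 × 0.01 × 4 = 20 ruptures, far below 130.

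The article does not show how 500 was derived, but the figure fits selection on rupture status. More than one image may then be on file for a patient, and the rule for choosing among them matters.

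**3. How far apart are the candidate times?**

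Assume a constant hazard over 4 years (1460 days) and visits exactly at 0, 90, 180, 365, 730, 1095 and 1460 days.

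- Mean time from entry to rupture: 1460 / 2 = 730 days.
- Mean time from last visit to rupture: Σ(gap²/2) / 1460, with gaps of 90, 90, 185, 365, 365 and 365 days. That is (8100 + 17112.5 + 199837.5) / 1460 = 154 days.

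The entry value and the last pre-rupture value are therefore about 576 days apart on average (730 − 154).

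**4. What a shift would do**

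The documents give no figure for change before rupture, so the shift *s* is an assumption. It is the net movement of ruptured cases away from comparators, in SD units, for a normal predictor with equal variances.

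- Apparent OR per SD = exp(ln OR at entry + *s*)
- Apparent AUC with no association at entry = Φ(*s*/√2)

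| *s* (SD) | OR if entry OR is 1.0 | AUC if entry OR is 1.0 | OR if entry OR is 1.5 |
|---|---|---|---|
| 0 | 1.00 | 0.50 | 1.50 |
| 0.25 | 1.28 | 0.57 | 1.93 |
| 0.5 | 1.65 | 0.64 | 2.47 |
| 1.0 | 2.72 | 0.76 | 4.08 |

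The table shows how sensitive the result is to timing. It does not estimate the bias in this study.

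**The case against.** The strongest reply is that Data collection and management is the section that governs measurement, and it can be read as placing HRMRI, CFD and laboratory data at entry. The Abstract sentence may be loose wording, and the Model building sentence is too garbled to carry much. Acquiring imaging data may simply mean retrieving stored files. An article also condenses, and the index date for controls may be set in the full protocol.

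Much of this stands and limits the point. A reader might infer four stronger things, which the documents do not support:

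- **That predictors are definitely taken near rupture.** This rests on one unclear sentence, chiefly about hemodynamic imaging. HRMRI and blood are not tied to rupture anywhere.
- **That the model cannot predict at presentation.** If entry values are used, the problem does not arise. Germline variants do not change, and CIAP-1 clinical data are baseline data.
- **That post-rupture material enters the model.** Nothing says so, and participation ends at rupture. Tissue from ruptured walls belongs to a separate histopathology comparison.
- **That early ruptures have no usable data.** They have the entry angiography, and Model building accepts CTA, MRA or DSA for hemodynamics.

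What the reply does not remove is the contradiction. The article goes beyond leaving a detail to another document: it states times for its central predictors that disagree, and the prediction time is part of the design of a prediction model.

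**Conclusion.** The point holds as a contradiction over measurement time for HRMRI, hemodynamic, morphological and non-genetic biomarker predictors. If the Abstract and Model building are followed as written, ruptured aneurysms may be measured nearer the event than their comparators. Odds ratios and ROC cut-offs may then be inflated for use at presentation, and the validation group would not reveal it.

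The direction assumes that values in cases move further from the comparators as rupture nears; movement the other way would weaken associations. The size cannot be determined from the documents, and the odds ratios of 1.28 to 2.72 come from assumed shifts. The separation of about 576 days rests on a constant hazard and on-schedule visits.

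**What to change.** Reconcile the Abstract, Data collection and management, and Model building on one predictor time for ruptured and non-ruptured aneurysms:

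- Compute morphology and CFD from the angiography required for inclusion.
- Take HRMRI and biomarkers from the first-visit acquisition. If they are obtained only at follow-up, use the same scheduled visit for every patient and start prediction time there.
- Exclude from the model anything obtained at or after rupture.
- Report near-rupture images only in a separate analysis of change, with controls matched on time since entry.

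The cost is mainly wording and a rule for choosing among stored images and samples. Ruptures without a usable measurement at the common time drop out of that predictor's analysis. Under the constant-hazard assumption, a 90-day time zero would lose about 90/1460 = 6% of ruptures and a 365-day one 365/1460 = 25%, which favors an early visit. Apparent discrimination may be lower, but it will better reflect use at presentation.

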**Discussion:**

This study will explore the risk of rupture of aneurysms and develop a scientific multidimensional model for predicting rupture of unruptured intracranial aneurysms.

*Clinical Trials registration* A Study on a Multidimensional Prediction Model for Rupture Risk of Unruptured Intracranial Aneurysms (CIAP-2), NCT03133624. Registered: 16 April 2017. https://clinicaltrials.gov/ct2/show/NCT03133624

## Background

Intracranial saccular aneurysms are increasingly often being detected in clinical practice in parallel with the increasing frequency of performing computed tomography (CT) and magnetic resonance imaging (MRI). A recent cross-sectional study of community data showed that the prevalence of unruptured intracranial aneurysm (UIA) is as high as 7% [1] among 35–75-year-old individuals in China. The rate of rupture of such aneurysms was almost 1% in a Japanese study [2]. Although the incidence is low, the consequences of aneurysm rupture are serious, the mortality rate in the early stages of hemorrhage reportedly being 40% and the rebleeding rate as high as 60%–70% [2]. Some models for predicting enlargement and rupture of such aneurysms are currently available. However, one of these models is for assessing risk of rupture of bifurcation aneurysms and incorporates only a few indicators [3]. Another large study had some bias that made the external efficiency relatively low [4]. These results and models are difficult to incorporate into clinical practice. It is therefore essential to identify all risk factors and construct a more accurate model for predicting rupture of aneurysms in Chinese people that is simpler to use and more effective in clinical practice.

### Hemodynamic and HRMRI have been gaining increasing attention for predicting rupture of aneurysms

Hemodynamic studies of risk of rupture of aneurysms have shown that turbulence in the aneurysm cavity, strong jet blood flow, and high shear stress can result in changes in the shape of the aneurysm, resulting in a very low velocity region (located at the base of the aneurysm and daughter sac). In areas of low flow velocity and low shear stress, the aneurysm wall cells shrink and degenerate, resulting initially oozing and subsequently in rupture and frank bleeding [5–9]. However, hemodynamic studies have some limitations. For example, some studies have focused too much on computational analysis and lack prospective validation by biological and clinical outcomes. Therefore, studies of hemodynamic characteristics of intracranial aneurysms need to be combined with clinical cohort and pathophysiological studies to provide more comprehensive data.

High resolution magnetic resonance imaging (HRMRI) was first used to diagnose Takayasu arteritis. This modality, which provides resolution accuracy of up to about 78% [10] for the aneurysm wall and surrounding tissue, enabling assessment of the pathology of development of the aneurysm wall, has shown that thickening of the aneurysm wall often denotes infiltration by inflammatory cells, conferring a high risk of rupture [11]. Edjlali et al. [12] found that circumferential aneurysmal wall enhancement (CAWE) is more frequently observed in unstable intracranial aneurysms and can be used as a surrogate for inflammatory activity in the aneurysmal wall. Hu et al. [13] found that wall enhancement consistently and strongly correlates with symptomatic aneurysms. Therefore, wall enhancement that is detected by HRMRI may predict instability of an intracranial saccular aneurysm.

### In the future, progression of aneurysms may be explained on the basis of biochemistry via biomarkers and genetic factors

Indirect evidence from clinical findings has indicated that some genetic factors may be associated with rupture of intracranial aneurysms. Familial aneurysms account for 7%–20% [14] of all aneurysms. Previous studies of familial and sporadic aneurysms have found associations between many regions of genes or chromosomes and presence of aneurysms [15]. However, the results of a large twin study suggest that subarachnoid hemorrhages (SAH) are mainly of non-genetic origin and that environmental variance is greater than genetic variance in individuals with SAH [16]. It is yet to be proved that biological markers and genetic abnormalities can predict SAH in Chinese individuals. Thus, this study will seek to validate target genes and biomarkers that have been identified as possible risk factors by other researchers.

### Clinical factors are important in predicting rupture of aneurysms

There has been ongoing study of the occurrence and rupture of unruptured aneurysms. Studies have shown that up to 85%–90% of ruptured intracranial aneurysms are ≤ 10 mm in diameter [17–20]. It is inappropriate to recommend treatment for all small (< 7 mm) UIAs because treatment-related morbidity and mortality is close to being higher than the morbidity and mortality of aneurysm rupture. The only published lifelong follow-up study found that smoking and female sex are more serious prognostic factors than aneurysm size [21]. Many factors contribute to SAH, the three predominant risk factors being smoking, sex, and blood pressure [22]. Another prospective study [23] found that old age is also a risk factor for aneurysm rupture. The International Study on unruptured intracranial aneurysms [24] found that the 5-year cumulative rupture rates for patients with no history of SAH with aneurysms located in the internal carotid, anterior communicating, anterior cerebral, or middle cerebral arteries were 0%, 2.6%, 14.5%, and 40% for aneurysms smaller than 7 mm, 7–12 mm, 13–24 mm, and 25 mm or greater, respectively, compared with rates of 2.5%, 14.5%, 18.4%, and 50%, respectively, for the same size categories involving the posterior circulation and posterior communicating artery aneurysms. The location and size of an aneurysm thus have an obvious effect on risk of rupture, as has also been shown in another cohort study [2]. The level of evidence in the above two studies was relatively strong. However, because there was a bias in selection, the external validity of the study needs to be verified; additionally, the applicability of the findings of large studies to the Chinese population is unknown. Some studies in China have found that various morphological features of aneurysms are associated with their rupture. These include irregular morphology of a daughter sac and leaf segments, high aspect ratio (ratio of aneurysm height to neck width), and high size ratio (ratio of aneurysm size to parent artery size). Although these studies have enriched our understanding of factors influencing the risk of rupture of aneurysms, some of them are small single center and/or retrospective studies and thus provide a low level of evidence-based data. More importantly, at present, China does not have a high-level prediction model that integrates these factors. Thus, we plan to carry out a large prospective multicenter cohort study with wide coverage to investigate rupture-related factors in China.

## Methods and design

The Study on a Multidimensional Model for Predicting Risk of Rupture of Unruptured Intracranial Aneurysms (CIAP-2) is the second project of the China Intracranial Aneurysm Program and is managed by Beijing Neurosurgical Institute and Beijing Tiantan Hospital), which manages a prospective observational registry of patients with UIA who were enrolled in our 20 centers in China during the first CIAP. It is sponsored by the National Key Research Development Program of China. This study has been designed as a prospective, observational registry and the treatment of patients will not be influenced by their participation in this observational study. This study adheres to the ethical principles of the Declaration of Helsinki and Human Biomedical Research Ethical Issues and Policy Guidance. The Institutional Review Board of Beijing Tiantan Hospital, Capital Medical University has approved the study (KY2017-017-01). We will inform participating patients or their relatives that the privacy of their data will be protected. These know they can withdraw from the study at any time. The study has been registered at https://clinicaltrials.gov/ct2/show/NCT03133624.

### Aims

CIAP is a multicenter, large prospective study of intracranial aneurysms that has five different facets: CIAP-1 is for setting up and managing a UIA queue of 5000 individuals and calculating the annual rate of rupture of those aneurysms; CIAP-2 for exploring risk factors associated with aneurysm rupture and developing a multidimensional model for predicting aneurysm rupture; CIAP-3 for exploring antithrombotic therapy in patients with UIA complicated by ischemic cardio-cerebrovascular diseases; CIAP-4 for comparing treatment options for UIA-intervention and craniotomy, the study protocol of CIAP-4 has been published [25]; and CIAP-5 is for development of standardized treatments for early-stage bleeding from aneurysms. CIAP-1 is responsible for the management of the UIA queue. This is for the second observational study. An overview of the CIAP design is presented in Fig. 1.

